**Baseline (t=0): directly before the decision aid**			
	Demographics	Age, gender, education [52]	Sample description, attrition analyses, covariate(s) in (main) analyses
	Smoking behavior	Smoking status, motivation to quit, type of tobacco products, amount of tobacco consumption, amount of past cessation attempts, and cessation assistance utilization in the past 6 months [52]	Sample description, attrition analyses
	Nicotine dependence	Revised Fagerström Test for Nicotine Dependence (FTND-R) [53]	Sample description, attrition analyses, covariate in (main) analyses
	Productivity loss	iMTA Productivity Cost Questionnaire (iPCQ) [54]	Economic evaluation
	Health care utilization	Contacts with health care professionals (plus frequency) in the past 6 months, cessation assistance utilization (plus frequency) in the past 6 months [55]	Economic evaluation
	Quality of life	ICEpop CAPability measure for Adults (ICECAP-A) [56]	Economic evaluation
	Stages of decision making	Stage of Decision Making [57]	Sample description, attrition analyses, process information, covariate in (main) analyses

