Based on these limitations and the existing literature, an online DA, called “VISOR,” containing an explicit evidence-based VCM and tailored advice was developed that helps smokers to choose evidence-based cessation assistance tools. This DA was systematically developed and is currently being tested in a national randomized controlled trial (RCT) for its effect on individual decisional processes and smoking cessation attempts, as well as smoking abstinence compared to a DA without the explicit VCM component. Specifically, we aim to test the following hypotheses. 

H_1a/b/c_ is that a DA with an explicit VCM and tailored advice will lead to a statistically significant increase in smoking abstinence after 1 month (H_1a_), 6 months (H_1b_), and 12 months (H_1c_) compared to a DA without an explicit VCM and tailored advice: direct effect on smoking abstinence.

H_2a/b/c_ is that a DA with an explicit VCM and tailored advice will lead to a statistically significant increase in evidence-based cessation assistance use after 1 month (H_2a_), 6 months (H_2b_), and 12 months (H_2c_) compared to a DA without an explicit VCM and tailored advice.

H_3a/b_ is that the positive effect of a DA with an explicit VCM and tailored advice (vs a DA without an explicit VCM and tailored advice) on smoking abstinence after 6 months and 12 months will be at least partially mediated by the use of evidence-based cessation assistance at 1-month (H_3a_) and 6-month (H_3b_) follow-ups, respectively: indirect effect on smoking abstinence.

H_4_ is that a DA with an explicit VCM and tailored advice will lead to a statistically significant decrease in decisional conflict (state of uncertainty about which course of action to take) right after the DA compared to a DA without an explicit VCM and tailored advice.

In addition, it will also be tested whether the DA is more cost-effective compared to a DA without the explicit VCM component. This paper aims to thoroughly describe the DA “VISOR,” its development process, and the study protocol to test its (cost-)effectiveness.

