#### Analysis of Primary and Secondary Outcomes

To assess the effects of the DA on dichotomous and continuous (primary and secondary) outcome measures, logistic and linear regression analyses will be conducted, respectively. Mediation analyses will be conducted to determine whether the effects of the DA on smoking abstinence are mediated through cessation assistance use. All analyses will include covariates that were selected a priori (as recommended by Gruijters [68] and De Boer et al [69]), if these are also associated with the 3 outcome measures as described in our hypotheses (ie, smoking abstinence, evidence-based cessation assistance use, and decisional conflict) within our sample. Demographic factors (ie, age, gender, and education) were selected for all 3 outcome measures. The Revised Fagerström Test for Nicotine Dependence was also selected for the smoking-related outcome measures, whereas stage of decision making was selected for decisional conflict. More information on the rationale for selecting those covariates can be found in Multimedia Appendix 1*.* Results will be reported from both the fully adjusted as well as crude analyses [68]. These analyses as well will be done with R [66], making use of the integrated development environment RStudio [67]. To test the robustness of the results, all analyses will be conducted according to 3 different approaches (if applicable): analyses based on (1) worst case scenario (dropout respondents are considered not to have changed), (2) multiple imputations, and (3) complete cases only. We will also test whether selective dropout has occurred in order to subsequently minimize the bias that this can cause.

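### The H3 mediation models omit baseline motivation, past quit attempts and prior assistance use, so the path from assistance use to abstinence is open to confounding of unknown sign and size

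*Protocol article*

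**What the plan says.** All places are in the protocol article.

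- **Table 3, baseline (t=0).** The smoking behaviour row includes motivation to quit, "amount of past cessation attempts, and cessation assistance utilization in the past 6 months". Its purpose is sample description and attrition analyses, nothing more. Nicotine dependence, in the next row, is marked "Sample description, attrition analyses, covariate in (main) analyses". Demographics and stage of decision making also carry a covariate role. Prior assistance use appears again under health care utilization, for the economic evaluation.
- **Analysis of Primary and Secondary Outcomes.** The a priori covariates are named for all analyses: "Demographic factors (ie, age, gender, and education) were selected for all 3 outcome measures"; the revised Fagerström test "was also selected for the smoking-related outcome measures, whereas stage of decision making was selected for decisional conflict". A selected covariate enters a model only "if these are also associated with the 3 outcome measures as described in our hypotheses" within the sample.
- **The same section, on H3.** "Mediation analyses will be conducted to determine whether the effects of the DA on smoking abstinence are mediated through cessation assistance use".
- **Introduction, hypotheses.** Under H3 the effect on abstinence "will be at least partially mediated by the use of evidence-based cessation assistance at 1-month" for the 6-month outcome, and by 6-month use for the 12-month outcome. Under H2 the decision aid "will lead to a statistically significant increase in evidence-based cessation assistance use after 1 month", and likewise at 6 and 12 months. H1 is labelled a direct effect on abstinence.

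**The concern.** Randomisation makes the arms comparable. It does not make users and non-users of assistance comparable within an arm. The second leg of H3 compares exactly those groups, so any baseline characteristic that drives both use and abstinence distorts it unless it is in the model.

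The protocol itself links two of the omitted variables to the mediator. Table 1 justifies the motivation criterion by saying that unmotivated smokers would not consider assistance. Steps 3 and 5 of the decision aid, and the section on its theoretical background, use past failed attempts to decide who is advised to combine methods. These variables bear on the choice of assistance, are in the data, and stay out of the model where that choice is the mediator.

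At stake is the interpretation of H3: mediation could be reported where use does nothing, or missed where it matters. The retention rule adds to this. A confounder whose association with an outcome is not detected in the sample is dropped, although its absence can still bias the indirect effect.

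**Working it through.** **1. Is the omission a stated choice?** Table 3 gives the smoking behaviour row no covariate role, and the analysis section names the covariates without these variables. The two places agree. The article describes the appendix, which is not shown, as the rationale for the covariates selected, so it gives no sign of a longer list.

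**2. The plan's own figure.** The plan gives no number for this point. The sample size is used below only as *n*. With 20.2% vs 13.6%, one-sided α 0.05, power 80% and pooled variance (mean proportion 0.169):

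n per arm = [1.645·√(2·0.169·0.831) + 0.842·√(0.202·0.798 + 0.136·0.864)]² / 0.066² = 397.6, so 398 per arm and 796 in total, as stated. Nothing here changes it.

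**3. What omission does when use has no effect.** None of the inputs is in the documents; all are assumptions. U is one standard normal baseline variable.

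- logit P(use) = −0.7 + 0.5·arm + ln(OR_u)·U
- logit P(abstinence) = −1.7 + ln(OR_y)·U, with no term for use
- Fitted model: abstinence on arm and use, without U
- Indirect effect = (arm difference in use) × (fitted risk difference, use vs no use)

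| OR_u / OR_y per SD | Arm difference in use, points | Spurious use-abstinence OR | Spurious risk difference, points | False indirect effect, points |
|---|---|---|---|---|
| 1.25 / 1.25 | 11.7 | 1.05 | 0.65 | 0.08 |
| 1.5 / 1.5 | 11.4 | 1.17 | 2.11 | 0.24 |
| 2 / 1.5 | 10.8 | 1.28 | 3.39 | 0.37 |
| 2 / 2 | 10.8 | 1.50 | 5.90 | 0.64 |
| 1.5 / 0.8 | 11.4 | 0.92 | −1.14 | −0.13 |
| 1.5 / 0.67 | 11.4 | 0.86 | −2.06 | −0.23 |

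Example, fourth row: 10.8 × 5.90 / 100 = 0.64. Simulation gives the same values within rounding (up to about 0.65). The last two rows show the reversal when a variable raises use but lowers abstinence.

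**4. Dependence on the arm difference.** The false indirect effect scales with it. At 4 points, the 1.5/1.5 and 2/2 rows give 4 × 2.11 / 100 = 0.08 and 4 × 5.90 / 100 = 0.24 points. At zero it vanishes.

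**5. Effect on the use-abstinence coefficient at n = 796.** A second simulation used about 30% use in control, 14% to 15% abstinence without assistance and an arm-to-use OR of 1.5. With no true effect of use, the two-sided 5% test of that coefficient rejected in 6.7%, 10.6% and 54.6% of trials for same-direction ORs of 1.25, 1.5 and 2. With U in the model it rejected in 4.4% to 4.9%. With a true use-abstinence OR of 1.5, the indirect effect was 0.60, 0.72 and 1.03 points without U, against 0.51 to 0.54 with U.

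**6. H2.** In the same setting the one-sided type I error was about 5% with or without U. Power without vs with U was 84% vs 85%, 82% vs 84% and 70% vs 77% for a predictor with OR 1.5, 2 and 3 per SD.

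**The case against.** The strongest reply is that direction and size are both assumed, and this stands. A reader might infer that H3 will tend to show mediation that is not there. The documents do not support that. The decision aid steers some smokers with failed attempts towards combined assistance. Only current smokers are eligible, so use in the past 6 months has not left them abstinent at entry. Either variable could go with more use and less abstinence, which reverses the bias.

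The size could also be smaller. Eligibility restricts the range of motivation. The planned covariates may absorb part of the confounding, and the calculation leaves them out. The Introduction reports that the earlier Dutch decision aid had no effect on assistance use, so an 11-point difference is not given. Even 0.64 points is about a tenth of the planning effect of 20.2 − 13.6 = 6.6 points (0.64 / 6.6 = 0.10). The 54.6% rejection rate belongs to the use-abstinence coefficient under the most extreme assumption, not to a test of the indirect effect.

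A reader might also infer that H2 is biased or ignores its own baseline value. Neither follows. Arm is randomised, so H2 is valid without the covariate. The baseline item is past-6-month use, whereas the outcome is the choice implemented after the decision aid: a close counterpart, not the same measure.

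Finally, an article may leave the mediation method and its sensitivity analyses to a fuller plan, so their absence is not the fault here. What remains is the covariate choice, which the article does fix.

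**Conclusion.** The point holds for H3. As written, the plan leaves three collected candidate confounders out of a comparison that randomisation does not protect, and its retention rule does not secure control of confounding. The bias is of unknown sign and size. Under the assumed same-direction associations it ranges from negligible (spurious OR about 1.05) to material (about 1.5; false indirect effect about 0.65 points with an 11-point arm difference in use). Under opposite-direction associations it is negative. H3 is therefore open to confounding; the documents do not show that it is confounded in a particular direction.

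For H2 the gain is precision only: about 1 to 2 points of power for a moderate predictor and about 8 for a strong one, under assumed associations. The H1 label is editorial. A regression on arm without the mediator estimates the total effect, and the planned analysis of H1 does not change. The primary comparison and the sample size are unaffected.

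**What to change.** 1. Pre-specify motivation to quit, number of past cessation attempts and assistance use in the past 6 months as covariates in both the mediator model and the outcome model of H3, retained whatever their association in the sample.
2. Update the purpose column of the smoking behaviour row in Table 3 to match.
3. Add a sensitivity analysis for unmeasured mediator-outcome confounding, since measured covariates cannot exclude it.
4. As a secondary improvement, add prior assistance use to the H2 models and describe it as a gain in precision.
5. Reword the H1 label to total effect.

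All variables are already collected at t=0. The cost is analysis wording, three further covariates in H3 and one in H2, best settled before outcomes are examined by arm.

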**Follow-up (t=1): directly after the decision aid**			
	Stages of decision making	Stage of Decision Making [57]	Sample description, process information
	Decision	Decision after having used the decision aid (DA), not yet implemented	Sample description, process information
	Decision-making process	Decisional conflict scale [58], first item from the Preparation for Decision Making Scale [59]	Hypothesis testing, H_4_ (decisional conflict scale [58]); process information and additional studies (see “Data Analysis”)
	Knowledge	Self-developed knowledge scale [60]	Additional studies (see “Data Analysis”)
	Perceived autonomy support	The Virtual Care Climate Questionnaire [47]	Additional studies (see “Data Analysis”)
	Perceived competence	Perceived competence scale [48]	Additional studies (see “Data Analysis”)
	Evaluation questions	Regarding attention, clarity, satisfaction, and one open question	Process information
	Recruitment channels	N/A^a^	Recruitment monitoring and analyses
**Follow-up (t=2): 1 month after baseline**			
	Decision implementation	Implemented decision (choice) after having used the DA	Hypothesis testing, H_2a_ and H_3a_
	Smoking (cessation) behavior	Prolonged abstinence; 7-day point prevalence abstinence; for users that did not successfully stop: type of tobacco products and amount of tobacco consumption [52]	Hypothesis testing, H_1a_ (7-day point prevalence abstinence [52]); additional studies (see “Data Analysis”)
	Stages of decision making	Stage of Decision Making [57]	Sample description, process information
	Knowledge	Self-developed knowledge scale [60]	Additional studies (see “Data Analysis”)
**Follow-up (t=3): 6 months after baseline**			
	Decision implementation	Implemented decision (choice) after having used the DA	Hypothesis testing, H_2b_ and H_3b_
	Smoking (cessation) behavior	Prolonged abstinence; 7-day point prevalence abstinence; for users that did not successfully stop: type of tobacco products and amount of tobacco consumption [52]	Hypothesis testing, H_1b_ and H_3a_ (7-day point prevalence abstinence [52]); additional studies (see “Data Analysis”)
	Productivity loss	iPCQ [54]	Economic evaluation
	Health care utilization	Contacts with health care professionals (plus frequency) in the past 6 months, cessation assistance utilization (plus frequency) in the past 6 months [55]	Economic evaluation
	Quality of life	ICECAP-A [56]	Economic evaluation
	Decisional regret	Decision regret scale [61]	Additional studies (see “Data Analysis”)
**Follow-up (t=4): 12 months after baseline**			
	Decision implementation	Implemented decision (choice) after having used the DA	Hypothesis testing, H_2c_
	Smoking (cessation) behavior	Prolonged abstinence; 7-day point prevalence abstinence; for users that did not successfully stop: type of tobacco products and amount of tobacco consumption [52]	Hypothesis testing, H_1c_ and H_3b_ (7-day point prevalence abstinence [52]); additional studies (see “Data Analysis”)
	Productivity loss	iPCQ [54]	Economic evaluation
	Health care utilization	Contacts with health care professionals (plus frequency) in the past 6 months, cessation assistance utilization (plus frequency) in the past 6 months [55]	Economic evaluation
	Quality of life	ICECAP-A [56]	Economic evaluation
	Decisional regret	Decision regret scale [61]	Additional studies (see “Data Analysis”)
	Evaluation questions	Regarding perceived decision support	Process information

^a^N/A: not applicable.

Participants are invited to fill in each follow-up questionnaire if they made use of the entire DA, even when they skipped one of the other follow-up questionnaires. To avoid high drop-out rates, participants receive either 1 automatic reminder after a week (if they have not filled in the follow-up questionnaires at all) or 2 after 2 days and a week (if they already started filling in at least parts of the follow-up questionnaires). Participants that started using either the DA or started filling in the baseline questionnaire (t=0) without finishing it also receive 2 automatic reminders (after 2 days and a week). In addition, participants who took part in the last measurement receive €10 (US $11.84). A visual representation of the trial flow can be seen in Figure 4.

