### Study Comparator Group

Participants in the control group receive the same DA without an explicit VCM and tailored advice; thus, the DA includes the following steps: (1) information section, (2) optional knowledge quiz, (3) brief smoking assessment, (4) intuitive decision, (5) intermediate advice, and (8) access information. Steps 6 and 7 are skipped. The only other difference is that participants in the control group are not immediately directed towards the end after they have chosen to use no evidence-based cessation assistance to also provide them with a chance to reevaluate their choice. More information about the individual steps can be found under “Description of the DA.”

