### Trial Flow and Measurement Instruments

As participants register for the study via an online form, which includes their provision of informed consent and the creation of an account, participants are automatically randomized into 1 of the 2 groups (intervention or control group), allocating approximately 50% of respondents to either group. After this, they are asked to fill in the first part of the baseline questionnaire (t=0) consisting of 22-94 items (depending on the respective answers; eg, if the participants state that they have never attempted to cease smoking, no follow-up questions are posed), in which general demographic information (eg, age), smoking behavior, nicotine dependence, productivity loss, health care utilization, quality of life, and stages of decision making are assessed. Participants are excluded from the study if they indicate that they are <18 years old, do not smoke, are not motivated to stop smoking within 6 months, or only use e-cigarettes. Participants immediately receive access to 1 of the 2 DAs after being randomized, as this process is fully automated. After having accessed the DA, the second part of the baseline questionnaire is made available (t=1). The second part consists of 53-56 items regarding stages of decision making, the decision, the decision-making process, knowledge, perceived autonomy support, perceived competence, user evaluation, and recruitment channels.

One month after the baseline questionnaire (t=2), users are asked to fill in a short follow-up questionnaire consisting of 14-21 items regarding cessation assistance utilization, smoking cessation status, stages of decision making, and knowledge.

After 6 months (t=3) and 12 months (t=4), users are asked to fill in a longer follow-up questionnaire that consists of 16-88 items relating to cessation assistance utilization, smoking abstinence (7-day point prevalence abstinence and prolonged abstinence), and questions regarding smoking behavior for those that did not achieve smoking abstinence. Health care utilization, productivity losses, quality of life, and decisional regret are also assessed (again). During t=4, 2 qualitative items are included to assess users’ experience of having used the DA during their cessation attempt.

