## Results

The RCT started in January 2020, and at this writing, 1248 users created an account, of which 519 finished the DA. Data collection is ongoing and will be conducted until September 2021.

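### Participants are randomised at account creation but followed up only if they used the entire DA, so outcomes at 1, 6 and 12 months come from a post-randomisation subset that allocation can shape

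*Protocol article*

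**What the plan says.** In Trial Flow and Measurement Instruments, allocation takes place at online registration: "participants are automatically randomized into 1 of the 2 groups (intervention or control group), allocating approximately 50% of respondents to either group". The first questionnaire follows: "After this, they are asked to fill in the first part of the baseline questionnaire (t=0"). Eligibility is read from the participants' own answers ("Participants are excluded from the study if they indicate that they are <18 years old, do not smoke", with further criteria on motivation and e-cigarettes).  Table 3 places t=0 directly before the DA.

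The text under Table 3 sets the condition for follow-up: "Participants are invited to fill in each follow-up questionnaire if they made use of the entire DA". Having missed an earlier questionnaire does not stop later invitations. Table 3 takes the H1 to H3 outcomes from t=2, t=3 and t=4, and the post-baseline economic data from t=3 and t=4.

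The two DAs differ in length and routing. Description of the DA lists eight sections for the intervention. For control, Study Comparator Group says: "Steps 6 and 7 are skipped". The same section adds that control users who choose no evidence-based assistance are not sent straight to the end. Theoretical Background of the Different Sections says that intervention users who keep a non-evidence-based choice are sent there directly, and that those who keep a choice of no assistance go to step 8.

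Results reports the position at the time of writing: "1248 users created an account, of which 519 finished the DA". Analysis of Primary and Secondary Outcomes plans worst-case, multiple-imputation and complete-case analyses and a check for selective dropout.

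**The concern.** Finishing the DA happens after randomisation, and what has to be finished depends on the arm. Someone who stops during the value-clarification statements in the intervention arm is never asked about smoking or assistance use. A similar person in the control arm does not meet those statements, may finish, and is asked.

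The routing also depends on what the user intends to do. The intervention path is longer for people inclined towards evidence-based assistance and shorter, or at least no longer, for some who reject it. That inclination is closely tied to assistance use, which is the H2 outcome and the H3 mediator. Allocation can therefore change who is observed in a way related to outcome, and the observed groups need not be comparable even if randomisation itself worked perfectly.

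At stake are the primary outcome (7-day point prevalence abstinence), assistance use, the mediation analysis and the economic evaluation. A statistical analysis plan cannot recover outcomes that were never requested.

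**Working it through.** **1. The plan's own sample size.** Inputs from Required Sample Size: 20.2% vs 13.6%, one-sided α = 0.05, power 0.80. With pooled variance under the null and no continuity correction, p̄ = 0.169 and

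n = [1.645·√(2·0.169·0.831) + 0.842·√(0.202·0.798 + 0.136·0.864)]² / 0.066² ≈ 398 per arm.

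This matches the stated 398 (796 in total), and 796/0.5 = 1592 matches the recruitment target. The arithmetic is sound. The design effect for comparison is 20.2 − 13.6 = 6.6 points.

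**2. Completion so far.** 519/1248 = 41.6% finished and 58.4% had not, arms pooled.

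**3. Finishers only, no true effect.** Completion by arm is not given, so these inputs are assumptions. In both arms 40% of participants are highly motivated and quit at 22%, and 60% are less motivated and quit at 8% (overall 0.4·22% + 0.6·8% = 13.6%). The highly motivated finish either DA at 60%. The less motivated finish the control DA at 40%.

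Control finishers: (0.4·0.60·0.22 + 0.6·0.40·0.08)/(0.24 + 0.24) = 15.0%.

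| Less motivated who finish the intervention DA | Overall completion, intervention (control 48%) | Abstinence among intervention finishers | Spurious difference | One-sided type I error at 398 per arm |
|---|---|---|---|---|
| 40% | 48% | 15.0% | 0 | 5% |
| 30% | 42% | (0.0528 + 0.0144)/0.42 = 16.0% | +1.0 point | 10% |
| 20% | 36% | (0.0528 + 0.0096)/0.36 = 17.3% | +2.3 points | 23% |

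The error rate is 1 − Φ(1.645 − bias/SE). For the middle row, SE = √[(0.15·0.85 + 0.16·0.84)/398] = 0.0257.

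The sign depends on who is lost. Suppose instead that only the highly motivated were lost in the intervention arm, finishing at the same 40% as the others. Its finishers would then show (0.4·0.40·0.22 + 0.6·0.40·0.08)/(0.16 + 0.24) = 13.6% against 15.0%, a spurious −1.4 points.

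**4. Worst case over everyone randomised, no true effect.** If never-invited non-finishers are counted as smokers and 13.6% quit in both arms, the spurious difference is −0.136 × the completion gap (control minus intervention). Assumed gaps of 5, 10 and 15 points give −0.7, −1.4 and −2.0 points.

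**5. The planned analyses side by side.** Complete cases are finishers by construction. Worst case either omits non-finishers (step 3 applies) or counts them as unchanged (step 4 applies). Multiple imputation would have no observed outcome from any non-finisher, so it would have to carry finishers' outcomes over to non-finishers using data from before they stopped. The selective-dropout check can compare baseline characteristics, but not outcomes that were not collected.

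**The case against.** Several stronger readings are tempting, and the documents do not support them.

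- *The rule favours the intervention.* Steps 6 and 7 are not required of every intervention user, and some have a shorter path than control. Completion by arm is not reported, and if loss were proportional across types of participant the bias among finishers would be zero. The direction is open.
- *58% of participants go without follow-up.* The 1248 are accounts at one moment during data collection. They may include ineligible people, people who stopped during t=0 before seeing either DA, and people still in progress. Only losses that the DA content or routing can influence can differ by arm.
- *All planned analyses are restricted to finishers.* The article does not define who counts as a dropout. Worst case and imputation may take in non-finishers, the analysis set is commonly left to a SAP that is not shown, and Figure 4 is missing. Including non-finishers still does not supply their outcomes.
- *H4 is lost through the same rule.* Decisional conflict is measured at t=1, which the text calls the second part of the baseline questionnaire, opened once the DA has been accessed, while Table 3 labels it follow-up. It is not clear that the invitation rule applies to it.
- *Randomising before the eligibility check is itself a bias.* The exclusions are participant characteristics asked in the same way in both arms. Moving the allocation point now would create two differently randomised cohorts.

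What remains is the invitation rule. It is stated outright, it depends on an event after allocation, and that event is defined differently in the two arms.

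**Conclusion.** The point holds as a risk built into the design, not as a demonstrated bias. Outcome collection at t=2 to t=4 depends on finishing a DA whose content and routing differ by arm. With no true effect, the illustrations give about 0 to +2 points among finishers when loss falls on the less motivated, with the sign reversed when it falls on the highly motivated. Worst-case analysis of everyone randomised gives about −0.7 to −2 points for completion gaps of 5 to 15 points. Both are well below the 6.6-point design effect, but large enough to raise the one-sided 5% error to about 10% or 23% in the two unequal-completion scenarios. These figures rest on assumed strata, quit rates and completion gaps; only the 41.6% pooled completion, the 398 per arm and the 6.6 points come from the article. The matter should be settled while data collection is ongoing, because outcomes not requested on time cannot be recovered.

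**What to change.** 1. Delete the condition on having used the entire DA. Send t=2, t=3 and t=4 to every randomised participant who passed the t=0 eligibility questions. Include those already enrolled who stopped part-way, for time points not yet passed.
2. Make all eligible randomised participants, as allocated, the primary analysis set for H1 to H3 and the economic evaluation. Keep DA finishers as a secondary analysis. State that non-finishers count as missing when they do not respond.
3. Report DA completion by arm.
4. For H4, measured after the DA, report completion by arm alongside the result and state the dependence on it as a limitation.

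The allocation point need not move.

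Cost: a change to the automated invitation rule and a protocol amendment. A contact route already exists, since people who start the DA or t=0 without finishing receive two automatic reminders. The incentive adds up to EUR 10 per extra respondent at the last measurement. The downside is that non-finishers will probably respond less often, so the response rate will look lower and missing data will remain. However, some of their outcomes will be observed, and imputation will no longer rest on finishers alone.
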